### Primary Outcome Measure

The primary outcome measure for this study is the BOLD signal detected via fMRI in specific brain regions that are associated with motor, sensory, memory, and cognitive circuits elicited during both the rest and task phases. A 3-Tesla MRI scanner will be used to assess the brain’s response to different stimuli at multiple time points: before the *nasya karma* procedure, immediately before the *nasya karma* procedure, immediately after (within 15 min) the *nasya karma* procedure, and on the 14th day of the *nasya karma* therapy.

### Secondary Outcome Measures

These include the therapeutic effects of *marsha nasya karma* on cognitive function assessed via the Montreal Cognitive Assessment scale [11], perceived stress assessed using the Perceived Stress Scale [12], anxiety assessed using the Hamilton Anxiety Rating Scale [13], and health-related quality of life assessed using the 36-Item Short Form Health Survey [14]. The secondary outcomes will be assessed before the intervention and on the 1st and 30th days following the *nasya karma* therapy.

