**Methods:**

A total of 60 healthy volunteers in the age group of 20 to 40 years who fulfill the selection criteria will be recruited for this randomized controlled trial at the National Ayurveda Institute for Panchakarma, Cheruthuruthy, Kerala, India, and randomized in a 1:1 ratio to either the intervention group (n=30; group 1, receiving *nasya karma* with *anu taila*, an oil-based formulation manufactured using a paste and decoction of herbal medicines with oils as the base material, for a period of 14 days) or the control group (n=30; group 2, not receiving any intervention). The participants will undergo task-based and resting fMRI on day 1 (twice on day 1 before administration and 15 minutes after *nasya karma* for participants in group 1) and day 14 to map the neurophysiological response to *nasya karma* of the brain. A comprehensive neuroimaging protocol using structural magnetic resonance imaging and fMRI will be used in the study. The effect of *nasya karma* on sleep, psychological well-being, cognition, and quality of life will be assessed on the 1st and 30th days in both groups.

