### Interventions

The participants in the intervention group will be administered *nasya karma* (nasal instillation) with *anu taila* at a dose of 3 mL per nostril for 7 days (on every alternate day for 14 days) as indicated in the Ayurveda treatises for healthy individuals. Before *nasya*, local oleation and sudation of the head region will be conducted for approximately 10 minutes. Following the *nasya karma* procedure, participants will inhale medicated smoke and rinse their mouths with lukewarm water. The control group, consisting also of healthy individuals, will not undergo any interventions to facilitate assessment of the specific effects attributed to *nasya karma* in the intervention group when compared to baseline measures in healthy individuals.

*Nasya karma* will be administered by the investigator at the hospital’s *panchakarma* unit except on assessment days, when it will be conducted at AIMS. Each participant will be closely monitored for 30 minutes following the procedure to observe any immediate effects or reactions. Vital signs such as heart rate, blood pressure, and respiratory rate will be monitored and recorded before and after every session. Participants reporting any adverse symptoms experienced after each session will be recorded through a standardized format designed to capture a wide range of potential side effects, including nasal irritation, headache, dizziness, nausea, or any other discomfort. Any serious adverse event will be reported immediately to the institutional ethics committee, and a causality assessment will also be conducted. Appropriate care will be provided for all adverse events requiring medical intervention, and they will be followed up on until resolution or stabilization.

If a participant experiences significant adverse effects, such as severe nasal irritation, fever, sinusitis, or any other serious discomfort that impacts their well-being, the intervention will be immediately halted, and the participant will be withdrawn. Discontinuation will also occur in cases of noncompliance with the treatment regimen, if the participant wishes to withdraw for any reason, or if the participant meets any of the exclusion criteria during the study. As the trial involves healthy volunteers, administration of concomitant medication is prohibited during the trial period of 30 days.

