#### Statistical Analysis

##### Overview

The modified intention-to-treat principle will guide the analysis for all outcomes within the full analysis set. Quantitative data will be summarized using mean, SD, minimum, maximum, and median values. Enumeration data will be presented as frequency and the corresponding percentage. Intragroup comparisons will be conducted using the Student paired *t* test or Wilcoxon signed rank test for continuous variables and the chi-square test for categorical variables. Intergroup comparisons will be conducted using the independent-sample *t* test or the Mann-Whitney *U* test. Significance thresholds will be set at *P*<.05 for all 2-tailed tests.

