**Clinical assessment**							
	Group A						✓
	Group B						✓

^a^fMRI: functional magnetic resonance imaging.

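### The clinical scales are given three incompatible assessment schedules, and the one in Table 1 has no pre-treatment assessment

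*Protocol article*

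**What the plan says.** The article states the timing of the clinical scales in three places.

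- **Abstract, Methods:** the effects "on sleep, psychological well-being, cognition, and quality of life will be assessed on the 1st and 30th days in both groups". This is two assessments. It does not say whether the day-1 assessment comes before or after that day's nasya session.
- **Secondary Outcome Measures:** "The secondary outcomes will be assessed before the intervention and on the 1st and 30th days following the" nasya therapy. This is three assessments, two of them counted from the therapy. The section names four scales, covering cognition, perceived stress, anxiety and health-related quality of life.
- **Table 1 (Gantt chart):** the block headed "Clinical assessment" has one tick for Group A and one for Group B, both in the 30th-day column. Nothing is ticked at Week 0, on day 1 or on day 14.

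Three other statements bear on the point. Under Interventions, nasya is given "for 7 days (on every alternate day for 14 days"), and concomitant medication is "prohibited during the trial period of 30 days". The Overview of the Statistical Analysis section says "Intragroup comparisons will be conducted using the Student paired" *t* test or the Wilcoxon signed rank test. For comparisons between groups it plans the independent-sample *t* test or the Mann-Whitney *U* test.

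**The concern.** The three statements differ in the number of visits and in the day from which visits are counted, so staff using different parts of the article would collect different data. Two things are at stake.

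The first is the baseline. A paired within-group test needs a value taken before treatment. If the scales are not completed before the first nasya session, that value cannot be recovered later.

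The second is the date of the final assessment. Counting from the therapy gives a different day from counting from the start of the study. Controls have no therapy to count from. Neither participants nor assessors are blinded, so the timing of these scales should be fixed in advance and be the same in both arms.

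**Working it through.** There is no stated figure to reproduce. This is a consistency check with simple date arithmetic.

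**Step 1. Place the Table 1 ticks.** The rows were aligned to the header column by column. As a control, the fMRI rows of the same table were placed the same way. Group A falls on day 1, day 1 immediately after nasya, and day 14; Group B falls on days 1 and 14. Both agree with the abstract, so the alignment is sound. Both clinical rows then show a single tick, in the 30th-day column.

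**Step 2. Set the schedules side by side.**

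| Source | Assessments | Before treatment | Final assessment |
|---|---|---|---|
| Abstract | 2 | Day 1, order relative to nasya not stated | Day 30, both groups |
| Secondary Outcome Measures | 3 | Yes, stated | 30 days after therapy |
| Table 1 | 1 | None ticked | Day 30, both groups |

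**Step 3. Turn the dates counted from therapy into study days.** Seven sessions on alternate days from day 1 fall on days 1, 3, 5, 7, 9, 11 and 13, which matches the intervention period of days 1 to 13 in Table 1. Taking the end of therapy as day 13, or as day 14 if the full 14-day course is counted:

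- first day after therapy: 13 + 1 = day 14, or 14 + 1 = day 15;
- thirtieth day after therapy: 13 + 30 = day 43, or 14 + 30 = day 44.

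The later visit lies 43 − 30 = 13 to 44 − 30 = 14 days beyond the 30-day trial period, and as many days after the day-30 visit in the abstract and Table 1. The earlier visit, at day 14 or 15, has no clinical tick in Table 1 and is not in the abstract.

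**Step 4. Check the planned tests against each schedule.**

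- Secondary Outcome Measures: a pre-treatment value exists, so paired tests can be run.
- Abstract: paired tests of pre-treatment against day 30 can be run if the day-1 assessment precedes nasya, which is not stated.
- Table 1: one value per person, so no paired test can be run for any of the four scales (0 of 4 with a baseline on this schedule).
- Abstract and Table 1: both arms have a day-30 value, so the unpaired comparison between groups can be run.

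**The case against.** The strongest reply is that this is loose drafting around an evident intention. The Methods text states a pre-treatment assessment in so many words, and the abstract has an assessment on day 1. Two of the three sources therefore carry an early value, and only a summary chart omits it. Three sources also point to day 30: the abstract, the Table 1 column and the 30-day trial period. On that view the Methods sentence means before treatment and day 30 of the study.

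Much of this stands, and it rules out several stronger readings that a reader might infer.

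- **That the plan has no baseline, so change cannot be measured.** The documents do not support this. The loss occurs only if Table 1 is followed against the Methods text.
- **That the arms will be compared at different times, about day 43 against day 30.** No passage says so. The abstract and Table 1 both put the control group at day 30, and both put the nasya group there too. The literal Methods wording is at odds with them, but it does not establish a planned imbalance.
- **That a calculable amount of power is lost.** The one effect size in the article, 0.6 under Power Analysis, is for activation differences on fMRI. No baseline-adjusted comparison between groups is planned, and the Limitations say the design is not powered for clinical efficacy. There is no basis for a power figure on these scales.
- **That the planned correlations with fMRI fail.** They relate clinical measures to imaging metrics and do not specify clinical change scores.

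It could also be said that a tick was lost when the table was read from PDF. That cannot be fully excluded, but the fMRI rows of the same table are placed correctly. The abstract and the Methods section also disagree in plain prose, whatever the table shows.

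The charitable reading does not remove the conflict. The Methods sentence lists the pre-treatment assessment and the first-day assessment as separate occasions, and it counts the latter from the therapy. Nor is this detail that an article leaves to a fuller document, since the article states the schedule three times and differently.

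**Conclusion.** The schedule is wrong as written and must be reconciled. Three statements give two, three and one assessments, and they do not share a starting day. On Table 1 alone, none of the four scales has a pre-nasya value and the within-group paired tests cannot be run. Read literally, the last assessment in the Methods text falls at about day 43 or 44, outside the 30-day trial period and undefined for controls.

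The scope is limited. Only secondary outcomes are affected; the fMRI schedule in Table 1 agrees with the abstract. The day-30 comparison between randomised groups remains possible. The loss of the baseline is conditional on staff following Table 1. The date arithmetic assumes that sessions run on alternate days from day 1 and that therapy ends on day 13 or 14.

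**What to change.** Give one schedule, counted from a common study day for both arms, and state it identically in the abstract, the Secondary Outcome Measures section and Table 1.

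- In Table 1, tick the clinical assessment for Groups A and B at a pre-nasya baseline as well as at day 30. The baseline can be at Week 0 before randomization, or on day 1 before the first nasya session.
- In the Secondary Outcome Measures section, replace the timing relative to therapy with study days that also apply to controls. If an assessment near day 14 is intended, name the day and tick it for both groups.
- In the abstract, say that the early assessment precedes nasya.

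The two baseline options differ in one respect. Table 1 places randomization at Week 0, and participants open their own envelopes before enrollment, so a day-1 baseline would be completed with allocation already known. A Week 0 baseline before randomization avoids this.

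The cost is wording and ticks, plus the time to complete four scales at a visit both arms already have (screening at Week 0 or the scan on day 1). Neither option requires randomization to be moved.

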### Detailed Methodology of the Primary Outcome Measure

#### Overview

The primary outcome measure encompasses 2 key components. The first is the assessment of the immediate neurophysiological response elicited by *nasya karma* during both the resting and task phases using MRI. The second component is the evaluation of the neurophysiological response elicited by *nasya karma* after 14 days (following 7 days of nasya) during both the resting and task phases using MRI. Functional neuroimages will be collected using a 3-Tesla scanner (Discovery MR750w; GE HealthCare). Resting state fMRI data will include 3D T1-weighted structural imaging with a fast-spin echo sequence and BOLD imaging with a spin echo, gradient echo, and echo-planar imaging sequence for 40 minutes, covering the entire brain. The parameters for 3D-T1 imaging will include a slice thickness of 1 mm; a repetition time and echo time of 8.5 milliseconds and 3.2 milliseconds, respectively; a field of view of 256 × 256 × 142 mm^3^; a flip angle of 12°; a matrix of 256 × 256; an in-plane resolution of 1 × 1 × 1 mm^3^; and 142 layers. The parameters for BOLD imaging will include a slice thickness of 3.2 mm; a repetition time and echo time of 3000 milliseconds and 30 milliseconds, respectively; a flip angle of 80°; a matrix of 64 × 64; a field of view of 256 × 256 × 142 mm^3^; 35 layers; and 150 time points.

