### Objectives

The primary objective of this study is to investigate the neurophysiological activity of the brain induced by the *nasya karma* procedure using blood oxygen level-dependent (BOLD) fMRI to elucidate the comprehensive neural response to *nasya karma* both in the rest and task phases. The secondary objective is to examine the impact of the *marsha nasya karma* (Ayurveda nasal drug delivery using a medicated or nonmedicated lipid medium) procedure on health parameters in apparently healthy volunteers, such as quality of life; cognition; sleep; and psychological well-being through anxiety, stress, and cognitive health.

The research hypothesis for this study is that the administration of *marsha nasya karma* with *anu taila* will increase the activation of different brain areas and enhance functional connectivity in different neuronal networks compared to baseline.

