#### Preparatory Phase

Participants will undergo a robust screening interview to ensure understanding and absence of contraindications for MRI scanning. Before the task phase fMRI, participants will be thoroughly informed and trained. Communication with the operator will be maintained throughout the scan. Incidental findings requiring medical intervention will be disclosed, and participant comfort will be ensured during scanning. All scans will be reviewed by a qualified radiologist, and any clinically significant incidental findings will be communicated confidentially to the participant along with appropriate referral advice for further evaluation and management as per institutional protocols. Verbal communication will be limited due to MRI noise, and the participants will use a 4-button fiber-optic response box positioned for use with their right hand to communicate and record behavioral responses during tasks. To mitigate the effects of scanner noise, participants will wear earplugs. Head motion will be minimized using foam pads and a headband to ensure stable positioning throughout the MRI scans. Metallic items will be removed, and participants will wear MRI-compatible attire. Participants in both the trial and control groups will be directed to avoid heavy meals within 2 hours before and 1 hour after *nasya karma*. Both groups will refrain from consuming coffee, tea, or caffeinated drinks for 12 hours preceding the fMRI. In contrast, the control group will undergo resting state mapping on both the 1st and 14th days, whereas the participants in the intervention group will undergo the *nasya karma* procedure lasting approximately 30 to 45 minutes, after which participants will proceed to the MRI room. Participants in the control group will proceed directly to the MRI without any intervention.

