#### Data Collection

##### Resting Phase fMRI

In this study, a block design paradigm will be used during task phases before and after *marsha nasya karma*, where stimuli are presented continuously within specific blocks alternated with rest periods to elicit and distinguish brain responses. Resting state fMRI, on the other hand, captures spontaneous brain activity without external stimuli, allowing for the correlation of signal fluctuations among functionally related brain regions. Panbrain activation mapping will be conducted during the resting phase before and immediately after *nasya karma* therapy (within 15 min) in the trial group. fMRI will be conducted before the *nasya karma* procedure and then again after the complete procedure is over. Participants in the control group will proceed directly to fMRI. During scanning, participants will be instructed to remain still with their eyes closed for 15 minutes to avoid motion artifacts. Any head movement will necessitate repeat mapping. The resting state fMRI paradigm will map spontaneous brain activity across the visual, auditory, motor (left and right), memory, and language domains before and after *marsha nasya karma*.

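### The immediate response, one of two primary components, is measured only in the nasya group, so the day-1 change cannot be attributed to nasya

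*Protocol article*

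**What the plan says.** **Primary outcome.** The Overview under Detailed Methodology of the Primary Outcome Measure names two components. On the immediate one: "The first is the assessment of the immediate neurophysiological response elicited by *nasya karma* during both the resting and task phases using MRI". The other is the response at day 14, after seven nasya sessions.

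**Scan schedule.** The Abstract (Methods) has participants scanned on days 1 and 14, with the extra day-1 scan confined to one arm: "twice on day 1 before administration and 15 minutes after *nasya karma* for participants in group 1". Resting Phase fMRI places the resting pair "before and immediately after *nasya karma* therapy (within 15 min) in the trial group". Table 1 agrees: Group B has no tick in the column for the scan immediately after nasya.

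**Controls on scan days.** Preparatory Phase states: "Participants in the control group will proceed directly to the MRI without any intervention". It describes no second day-1 scan and no matched waiting period. The same section says that "the control group will undergo resting state mapping on both the 1st and 14th days", and does not mention task scans for controls there. The Abstract gives participants generally both task-based and resting fMRI.

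**Hypothesis and role of the controls.** Objectives predicts that nasya will increase activation and "enhance functional connectivity in different neuronal networks compared to baseline". Interventions says that the untreated group is there so that effects specific to nasya can be assessed.

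**The concern.** A response described as elicited by nasya needs a comparison with what the same people, or exchangeable people, would have shown without it. Randomisation provides that comparison only where both arms are measured. On day 1 the second scan exists in one arm only, so half of the primary outcome makes no use of the control group.

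The second scan differs from the first in more than nasya. It is a second run in the scanner and of the same task battery, and it comes after a procedure of 30 to 45 minutes. Habituation, practice, fatigue and drift over time could each move the BOLD measures. Missing control scans cannot be recovered at the analysis stage.

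Two related matters bear on day 14. The arms reach that scan with different numbers of earlier sessions. The text is also unclear on whether controls do the tasks at all.

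**Working it through.** **1. Sessions per arm (Abstract and Table 1)**

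| | Day 1, first scan | Day 1, after nasya | Day 14 | Total |
|---|---|---|---|---|
| Nasya (n=30) | yes | yes | yes | 3 |
| Control (n=30) | yes | no | yes | 2 |

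The trial has 30×3 + 30×2 = 150 sessions. Primary Outcome Measure lists time points both before and immediately before the procedure, but Table 1 and Resting Phase fMRI show one pre-scan, and that is what is counted here. A further pre-scan in the nasya group would not supply the missing control scan.

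**2. What the immediate component can be.** Two contrasts are available: nasya scan 2 minus nasya scan 1, or nasya scan 2 against control scan 1. Write N for the effect of nasya and R for the effect of having a second scan later the same day (repetition, elapsed time, fatigue). Each contrast estimates N + R. No control has a second day-1 scan, so R cannot be estimated. This needs no outside figure.

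**3. How much R could matter.** The document gives no value for R, so there is no figure of the plan's own to reproduce. The size is an assumption, shown as a range. Statistical Analysis names the paired t test for within-group comparisons and two-sided .05. Multiple-Comparison Correction sets an initial voxel threshold of .001.

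With N = 0 and R = δ SD of the within-person change, the paired t statistic is noncentral t with 29 df and noncentrality δ√30 = 5.477δ. Rejection probability = P(|T| > c), with c = 2.045 at .05 and 3.659 at .001. For δ = 0.3 the noncentrality is 1.643.

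| δ (assumed) | 0.1 | 0.2 | 0.3 | 0.4 | 0.5 |
|---|---|---|---|---|---|
| rejects at .05 | 8.3% | 18.5% | 35.5% | 56.3% | 75.4% |
| rejects at .001 | 0.3% | 1.1% | 3.6% | 9.7% | 21.1% |

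These are single-test rates. Cluster-level inference over the brain is a different calculation.

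**4. Day 14.** The nasya group is on its third session and controls on their second. If the extra session leaves a residual effect of d SD of the change score, the two-sample t statistic has 58 df and noncentrality d√(30/2) = 3.873d, with c = 2.002 at .05.

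| d (assumed) | 0 | 0.1 | 0.2 | 0.3 | 0.4 | 0.5 |
|---|---|---|---|---|---|---|
| rejects at .05 | 5.0% | 6.7% | 11.9% | 20.8% | 33.2% | 47.8% |

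The imbalance in sessions is certain. A bias follows only if d is not zero about 13 days later, and the document says nothing on that.

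**5. Controls' task scans.** The Abstract gives participants task and resting fMRI; Preparatory Phase names resting-state mapping for controls. If controls have no task scans, the task-phase primary outcome has no control at day 14 either. If they have them, that comparison is randomised.

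**The case against.** **The trial is exploratory.** It says so repeatedly, and a before-after reading matches its hypothesis. That justifies reporting the day-1 change. It does not justify wording it as caused by nasya in a primary component.

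**Between-group analysis is already planned.** fMRI Data Analysis does plan comparisons between the groups. That stands for day 14, and the fix builds on it. It cannot help on day 1, where controls lack the second scan.

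**Training before scanning reduces practice effects.** Preparatory Phase provides training before the task scans. It may make R smaller, but it does not make R estimable.

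**The error rates depend on the assumptions.** This stands. The shifts are assumed, and the .05 figures fall sharply at .001. Direction matters too: the hypothesis is increased activation, so habituation or fatigue that lowers activation would work against it. The tables show sensitivity and do not predict false findings.

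**Stronger readings that the document does not support.** A reader might infer that the unequal scan count does bias day 14; that would need a lasting effect of one extra session, which is neither stated nor quantified. A reader might count the heat and the medicated smoke as confounders; Interventions makes them part of the procedure, and Blinding says that the procedural effect is the target. A reader might conclude that controls certainly have no task scans; Preparatory Phase does not say that they have resting scans only, so the point is conditional.

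**Conclusion.** The point holds in this form. The immediate component is an uncontrolled one-arm contrast, and this follows from the stated schedule alone. It cannot separate nasya from repetition, elapsed time or fatigue, so attributing the day-1 change to nasya is unsupported. Setting the hypothesis against baseline leaves the randomised comparison unused where it is available.

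The size is unknown, because the document gives no repeat-scan effect. The illustrative range rests on an assumed 0.1 to 0.5 SD shift, no nasya effect, 30 people and one test at a time. The day-14 comparison remains randomised; its session imbalance is a possible source of bias and has not been shown to be an actual one. Whether the day-14 task comparison has a control depends on how the Abstract and Preparatory Phase are reconciled.

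**What to change.** 1. Name the between-group difference in change from the day-1 pre-scan to day 14 as the primary contrast, and restate the hypothesis as nasya versus control.
2. Report the day-1 change, after minus before, as a descriptive within-group result, without attributing it to nasya.
3. Reconcile the Abstract with Preparatory Phase so that it is clear that controls have the same rest and task battery on days 1 and 14.
4. State the three-versus-two session imbalance as a limitation of the day-14 comparison.

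Items 1, 2 and 4 cost only wording. So does item 3 if controls already do the tasks. If they do not, the tasks add 4.5 + 4 + 2×4.5 + 6.75 = 24.25 minutes to each control scan. The downside is that the immediate effect can no longer be claimed as a causal primary result.

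The direct remedy would be a second day-1 control scan at a matched interval. It would turn the immediate component into a randomised contrast and equalise sessions at three each, but it adds 30 sessions (150 to 180). It is not required for this fix. Having controls repeat the tasks outside the scanner would not replace it, because the scan counts would stay unequal.

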##### fMRI Data Analysis

The fMRI data will undergo preprocessing using either the Data Processing and Analysis for Brain Imaging or CONN toolboxes, which will encompass essential steps such as slice timing correction, realignment for motion correction, regression to remove confounding effects, normalization to a standard template, smoothing to enhance signal-to-noise ratio, detrending to remove low-frequency drifts, and filtering to focus on relevant frequency bands, aligning with established practices in the field. After data preprocessing, amplitude of low-frequency fluctuation, functional connectivity, and large-scale functional brain network analysis will be conducted to investigate the difference in neurophysiological responses between the groups. The results will be interpreted in the context of the experimental paradigm to elucidate neural correlates of the studied phenomena, providing insights into the effects of *nasya karma* on brain function. Voxels exhibiting expected time-course correlations (30-second periods) will receive high activation scores, whereas those showing no correlation or deactivation will receive lower or negative scores, respectively. MRI data analysis will use general linear models via statistical parametric mapping (SPM). fMRI data will be processed using MATLAB 2023 (MathWorks Inc).

Resting phase MRI data will be analyzed using software tools such as SPM, the CONN toolbox, and the Functional Magnetic Resonance Imaging of the Brain Software Library (Analysis Group), whereas task phase fMRI will specifically use SPM. Given the focus on group data in this study, complex patterns of brain activation will be interpreted collectively rather than individually. For voxel-based analysis, a significance threshold of *P*<.01 at the voxel level and *P*<.05 corrected for false discovery rate (FDR) at the cluster level will be applied. Connectome-based analysis will use a threshold of *P*<.05 corrected for FDR. Additionally, Pearson correlation analysis will be performed to explore potential associations between clinical outcomes and fMRI findings, examining changes in brain activity following different interventions.

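### The immediate response, one of two primary components, is measured only in the nasya arm, so it has no concurrent control and cannot be attributed to nasya karma as worded

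*Protocol article*

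**What the plan says.** The Overview under Detailed Methodology of the Primary Outcome Measure names two primary components, each covering rest and task. On one: "The first is the assessment of the immediate neurophysiological response elicited by" nasya karma. On the other, after 14 days: "The second component is the evaluation of the neurophysiological response elicited by" nasya karma.

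The scan schedule appears in four places.
- Abstract, Methods: "The participants will undergo task-based and resting fMRI on day 1 (twice on day 1 before administration and 15 minutes after" nasya karma, with the repeat confined to group 1, and again on day 14.
- Table 1: group A is ticked on day 1, on day 1 immediately after nasya, and on day 14. Group B is ticked on day 1 and day 14 only.
- Resting Phase fMRI: "Panbrain activation mapping will be conducted during the resting phase before and immediately after" the therapy, in the trial group.
- Preparatory Phase: "the control group will undergo resting state mapping on both the 1st and 14th days". It names no task scans for controls. For the nasya arm it describes a "procedure lasting approximately 30 to 45 minutes, after which participants will proceed to the MRI room".

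On the role of the control group, Interventions says that it helps to assess effects specific to nasya. The design paragraph that introduces Figure 1 says that effects are evaluated against a control group. fMRI Data Analysis says that the imaging measures serve "to investigate the difference in neurophysiological responses between the groups".

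**The concern.** A statement that a response is elicited by a procedure is causal. In a randomized trial, support for it comes from comparing the change in the treated arm with the change over the same interval in the control arm. For the immediate component no such control change is collected.

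On day 1 a group 1 participant completes a session, undergoes a procedure of 30 to 45 minutes, and repeats the session. Any shift between the two scans mixes the effect of the procedure with second-session effects: familiarity with the tasks, habituation to the scanner, fatigue and elapsed time. The plan offers nothing with which to separate them.

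At stake is what the trial may conclude from one of its two primary components. Anticipated Findings expects distinct activation patterns within 15 minutes, and Strengths and Limitations counts the immediate mapping among the key features. The limitations listed there do not mention the missing control.

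**Working it through.** **1. Sessions per arm (Abstract, Methods; Table 1).**
- Nasya arm: day 1 before + day 1 after + day 14 = 3.
- Control arm: day 1 + day 14 = 2.
- Total planned: 30 × 3 + 30 × 2 = 150.

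**2. Contrasts available.**

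| Component | Nasya arm change | Control arm change | Randomized contrast of change |
|---|---|---|---|
| Immediate (day 1) | 30 pairs planned | 0 pairs | none |
| Day 14 versus day-1 pre-procedure scan | 30 pairs planned | 30 pairs planned | yes |

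Setting the nasya arm's post-procedure scan against the controls' only day-1 scan is possible, but it compares a second session with a first.

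**3. What is repeated.** Task durations from the task sections: visual 4:30, auditory 4:00, motor 2 × 4:30 = 9:00, memory 6:45. Sum: 4:30 + 4:00 + 9:00 + 6:45 = 24:15. With 15 minutes of eyes-closed rest (Resting Phase fMRI) the session is 39:15. The nasya arm goes through this twice on day 1.

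**4. Illustration of sensitivity.** The document gives no repeat-session effect. Assume a shift of h SDs of the within-person change and no nasya effect. The two-sided paired t test with n = 30 then follows a noncentral t with 29 degrees of freedom and noncentrality h√30. Chance of rejection for a single test:

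| h (assumed) | at 0.05 | at 0.001 |
|---|---|---|
| 0 | 5.0% | 0.1% |
| 0.1 | 8.3% | 0.3% |
| 0.2 | 18.5% | 1.1% |
| 0.3 | 35.5% | 3.6% |
| 0.5 | 75.4% | 21.1% |

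The 0.05 column matches the general threshold in the Statistical Analysis Overview. The 0.001 column matches the initial voxel threshold in Multiple-Comparison Correction. Neither is a whole-brain error rate: the cluster-level step needs spatial inputs that the document does not give. The table shows only that a modest repeat effect, if present, would be read as a nasya effect more often than the nominal level.

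**5. Do controls perform the tasks?** The Abstract describes task and resting scans for participants in general. The Preparatory Phase names resting-state mapping alone for controls. Under the Abstract, the day-14 task comparison exists and sets a third session against a second. Under the literal Preparatory Phase text, controls have no task data, and no between-group task comparison exists at day 14 either.

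**6. A further ambiguity.** Primary Outcome Measure lists both a time point before the procedure and one immediately before it. Table 1 shows one pre-procedure scan. If two were meant, the count would be 4 versus 2.

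**The case against.** The strongest defence is that the before-after design is disclosed. The hypothesis in Objectives is worded against baseline, the Statistical Analysis Overview plans paired tests within groups, Resting Phase fMRI openly confines the before-after mapping to the trial group, and the trial is labelled exploratory. All of that stands, and it makes an uncontrolled component permissible. It does not make the causal wording supportable, nor does it fit the stated purpose of the control group.

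Three stronger readings are tempting, and the documents do not support them.
- A reader might infer that the analysis section promises a between-group contrast for the immediate component that cannot be computed. That sentence is general, names no time point, and is satisfied by the day-14 scans.
- A reader might infer that the day-14 comparison is biased by the extra session. That requires an effect of one additional run to persist for about 13 days (day 1 to day 14). The visual and auditory paradigms are passive, the motor task is simple, and the resting measures involve no task; only the memory task is plainly sensitive to practice. The Preparatory Phase also provides for training before the task scans. Carry-over is possible but not shown.
- A reader might take the rejection rates at 0.05 as false-positive rates for the primary outcome. They are not: the imaging inference uses voxel and cluster thresholds, and the shifts are assumed.

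**Conclusion.** The point holds for the immediate component. On the document's own schedule 0 of 30 controls have an immediate before-after pair, so that component has no concurrent control, and a change in group 1 cannot be assigned to nasya karma rather than to repetition, fatigue or time. This conclusion rests on a count of scans and needs no assumption. The amount of distortion is unknown.

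The day-14 component does allow a randomized comparison of change, for resting measures on either reading of the control schedule. For task measures it does so only if controls perform the tasks, which the document leaves unsettled. If they do, the difference of 3 versus 2 sessions is a possible limitation of unquantified size, not a demonstrated bias.

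**What to change.** 1. In Primary Outcome Measure, in the Overview of its detailed methodology, and in fMRI Data Analysis, state that the immediate component is a descriptive within-group change in group 1 without a concurrent control, and remove causal wording for it.
2. In the same places, state that any claim that nasya karma changes brain function rests on the randomized between-group comparison of change from the day-1 pre-procedure scan to day 14.
3. Reconcile the Preparatory Phase with the Abstract on whether controls have task scans. If they do not, say that no between-group task comparison is available. Clarify at the same time whether Primary Outcome Measure means one or two pre-procedure scans.
4. If controls do perform the tasks, add the extra day-1 session in the nasya arm (3 versus 2) to Strengths and Limitations.

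These are changes of wording and cost almost nothing in resources. The price is scientific: the immediate result becomes descriptive.

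A second day-1 control scan after a matching interval would be the full remedy, because a repeat effect common to both arms would then cancel. It adds 30 sessions (150 to 180), may come too late given results expected in 2026, and is optional. Having controls repeat the tasks outside the scanner would be only partial: it leaves the immediate component uncontrolled and, with a 30 to 45 minute wait plus 24:15 of tasks, takes about 54 to 69 minutes per control participant.
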